### Recruitment and procedures

The potential participants will be enrolled from a tertiary-level general hospital in Shaanxi, China. The hospital is an essential medical resource in Northwest China, and the affiliated hospital of a well-known medical university with a profound history and accumulation in China. It has a large cancer center and provides continuous care from the inpatient to home-based interval chemotherapy periods for more than 3000 BC patients annually. We will contact participants in two main ways, the first being through active contact. Second, posters will be placed in waiting rooms and examination rooms at the oncology department or breast surgery department of this hospital, advertisements will be posted on the department’s official website, WeChat public account, video platform, etc., or word of mouth will be used. Interested women will be asked to contact research members via phone, email, or WeChat for detailed information. Regarding the second approach, researchers will learn about potential participants who meet the requirements through recommendations from health care staff in the department. After obtaining informed consent, the research team members will obtain the patients’ names and numbers, contact the patients to introduce the specific purpose and process of this study, and then ask them about their willingness to participate.

### Participant eligibility

The inclusion criteria for female patients are as follows: (1) aged ≥ 18 years, have been diagnosed with malignant BC by pathological examination and are aware of their disease and treatment; (2) have an order for chemotherapy and a regimen that has been established by oncologists according to their condition; (3) will be undergoing or receiving adjuvant or neoadjuvant chemotherapy; (4) have not yet initiated the early or middle stage of chemotherapy (for patients with a total of 4 chemotherapy cycles who have not yet had their first or second admission for chemotherapy; for a total of 6 cycles who had not yet had her the first, second, third or fourth admission chemotherapy; for a total of 8 cycles who had not yet had her the first, second, third, fourth or fifth or sixth admission for chemotherapy); (5) are able to orally feed themselves independently; (6) have no need for additional enteral or parenteral nutrition support after evaluation by the oncologists and dieticians; (7) can speak and understand Chinese, are aware of this research and agree to participate voluntarily; and (8) have good physical and mental status to support the progress of the intervention. The exclusion criteria are as follows: (1) end-stage cancer, such as systemic lymph node metastasis, a predicted survival of less than 6 months; (2) malignant tumors at other sites; (3) a plan to become pregnant, current pregnancy or becoming pregnant within 6 months after delivery; (4) family disagreement with study participation; (5) a history of psychiatric illness, severe cognitive impairment or severe visual, hearing or language impairment; (6) a poor nutritional status or pathological eating disorder, morbid obesity, etc.; and (7) participation in similar research.

### Sample size

G power software will be used to calculate the sample size of the study, and ANOVA and a priori power analysis were selected [27]. Because there is little relevant literature and most multidisciplinary health management interventions do not report detailed sample size calculation parameters, we adopted system default parameters, including an effect size of 0.25, a power of 0.95, and an α of 0.05. After calculation, the total sample size was 72, with 36 participants in each group. Considering a 20% loss-to-follow-up rate, we obtained a final sample of 44 participants per group.

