### Randomization

We seek to enroll 88 eligible BC patients during a 3-month recruitment period. The patients will be provided identifiers based on the enrollment order and will be randomly assigned to the intervention or usual groups. A random number Table [28] will be used to divide the 88 patients into two groups at a 1:1 ratio. We will start from the numbers in row 5 and column 6 of the random number table, and random numbers will be selected in turn from left to right. If the exact number is encountered, it will be skipped, and the following number will be skipped until 88 different numbers are collected. All the numbers will then be arranged from small to large, with patients with 44 smaller numbers assigned to the control group and those with the 44 larger numbers assigned to the intervention group. The random sequence will be unknown to the remaining research members except the statistician.

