### Statistical analysis

We will use IBM SPSS Statistics 21.0 software to analyze the statistical data. Descriptive statistics, such as the number of patients with different ages, education levels, cancer stages and types of chemotherapy, as well as the percentage of patients in different groups relative to the total number of patients, will be calculated for different groups of demographic and clinical information. The mean and standard deviation will be used to compare the DMBQ total and dimensions scores, the SUPPH and FACT-B scores, and BMI. To compare the baseline balance between the two groups, two independent sample *t* tests, chi-square tests or Mann‒Whitney U tests, will be used, depending on whether the data distribution satisfies homogeneity of variance. The Shapiro‒Wilk test will be used to verify whether the scores of the two groups at different time points follow a normal distribution. If the data are balanced, repeated ANOVA will be adopted. Otherwise, we will use a generalized estimating equation (GEE) to analyze the intervention’s time, group, and interaction effects [36]. For all the above tests, *P* < 0.05 will indicate a statistically significant difference, the α level will be 0.05, and the tests will be two-sided. We will use intention-to-treat (ITT) analysis to minimize bias for sensitivity analysis [37]. The results of the last measurement of the patients who drop out of the study will be taken as the effect, which assumes that they complete the intervention, and the analysis will be reconducted with the GEE. Furthermore, missing data will be imputed with the mean values of the characteristics or with the help of multiple imputation methods if they are random and unrelated to the research elements.

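### Enrolling 44 per group does not leave the required 36 after the planned 20% loss to follow-up; 45 per group would

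*Protocol article*

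**What the plan says.** The Sample size section of the protocol article reports a G*Power calculation in which "ANOVA and a priori power analysis were selected", with "an effect size of 0.25, a power of 0.95, and an α of 0.05". The result is given as follows: "After calculation, the total sample size was 72, with 36 participants in each group". The dropout allowance comes next: "Considering a 20% loss-to-follow-up rate, we obtained a final sample of 44 participants per group". No inflation formula is printed.

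The Randomization section carries the result forward: "We seek to enroll 88 eligible BC patients during a 3-month recruitment period". The allocation procedure is built on that number, using a random number table to "divide the 88 patients into two groups at a 1:1 ratio". The abstract also gives 88. No other part of the article states a different loss rate or enrolment target.

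**The concern.** A loss-to-follow-up rate is a proportion of the patients enrolled. To finish with a required number after a 20% loss, that number has to be divided by 0.8. Multiplying it by 1.2 adds 20% of the smaller, final number, and this is always too little. The printed 44 looks like the result of multiplying.

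The stated power of 0.95 belongs to 72 patients. If enrolment is too low for the plan's own loss rate, the trial ends with fewer than 72 when everything goes as assumed, and the sentence that justifies 88 is untrue. Follow-up runs to 12 months after the intervention, so the loss allowance will probably be drawn on.

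**Working it through.** **Inputs**

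| Input | Value | Source |
|---|---|---|
| Required after loss | 36 per group, 72 in total | Sample size |
| Assumed loss to follow-up | 20% | Sample size |
| Stated enrolment per group | 44 | Sample size |
| Stated enrolment in total, 1:1 | 88 | Randomization |

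**Step 1. Reproduce the plan's figure.** Multiplying, n × (1 + d) = 36 × 1.2 = 43.2, rounded up to 44 per group, and 2 × 44 = 88. This matches the printed numbers exactly.

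**Step 2. Inflate so that 36 remain.** Dividing, n / (1 − d) = 36 / 0.8 = 45 per group, and 72 / 0.8 = 90 in total. The result is a whole number, so rounding cannot turn it into 44.

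**Step 3. Apply the stated loss to the stated enrolment.**
- Per group: 44 × 0.8 = 35.2, below 36.
- In total: 88 × 0.8 = 70.4, below 72. The shortfall is 72 − 70.4 = 1.6, about two patients.

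**Step 4. Find the loss that 88 can absorb.** 1 − 72/88 = 16/88 = 18.2%. In whole patients, each group of 44 can lose 8 (8/44 = 18.2%) and keep 36. A ninth loss leaves 35.

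**Step 5. Effect on power.** The article does not give the ANOVA sub-type, the number of measurements or the correlation between them, so the settings below are assumptions. Both use two groups, effect size f = 0.25, α = 0.05 and zero correlation between measurements. They were chosen because each gives 72 as the smallest even total that reaches power 0.95.

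| Assumed setting | Power at 72 | Power at 70 |
|---|---|---|
| Between-group effect, 3 measurements | 0.952 | 0.946 |
| Group-by-time interaction, 4 measurements | 0.956 | 0.950 |

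Over the wider set of settings tried (ANOVA variants with 2 to 6 measurements and correlations of 0, 0.3 and 0.5), going from 72 to 70 patients costs at most about 1.3 percentage points of power.

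**The case against.** The arithmetic is not in dispute. The case on the other side concerns its weight, and has four parts.

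- **Size.** The gap is 2 patients in 90, or 2.2%, and the power cost is about one percentage point at most. No design decision would turn on it. This stands, and it makes the point a small correction.
- **The base of 72 is itself uncertain.** It comes from software default parameters, and the ANOVA settings are not printed. With six time points and an assumed correlation of 0.5, the same effect size, power and α give a total of about 28 for the group-by-time interaction or about 124 for the between-group effect. A two-patient shortfall is small beside that range. This also stands, but it is a separate matter: 72 is the number the plan says it needs, and 88 does not deliver it at the plan's own loss rate.
- **The formula is inferred.** The article does not say that it multiplied by 1.2. That is correct, although the match is exact. The error does not depend on the inference, because 20% loss from 44 leaves fewer than 36 however the 44 was reached.
- **Patients lost to follow-up may still contribute.** The Statistical analysis section plans last-measurement carry-forward with GEE, GEE as the alternative to repeated-measures ANOVA, and imputation under stated conditions. So the number contributing to a given analysis could exceed 70. This answers the point only in part. Carry-forward belongs to the sensitivity analysis, a standard repeated-measures ANOVA uses only patients with complete measurements, and imputation does not restore the lost information in full. None of these makes 20% loss from 88 leave 72 patients.

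**Conclusion.** The concern holds. The required number, the loss rate and the enrolment figure are all printed, and they are inconsistent: 44 per group with 20% loss leaves about 35 per group and 70 in total, where 36 and 72 are required. The matching enrolment is 45 per group, 90 in total. The 88 planned patients cover a loss of up to 18.2%.

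This conclusion rests only on reading the 20% as a share of those enrolled and on taking 72 as the number needed after loss. The practical effect is slight: about two patients, and a power loss of at most about 1.3 percentage points under the assumed ANOVA settings. It is an arithmetic slip in the figure that sets enrolment. It should be corrected, but it does not threaten the trial.

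**What to change.** Change one sentence in the Sample size section, in one of these ways:

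1. Keep 88 and state that it allows for up to 18% loss to follow-up. This costs nothing in patients and remains possible after recruitment has closed. The authors should be open that 18% is what 88 can bear, since the article gives no evidence for 18% over 20%.
2. Keep 88 and the 20% assumption, state that about 70 patients would then remain, and report the power for 70. This needs no extra patients either, but the authors must first give the ANOVA sub-type, number of measurements and correlation behind the 72.

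If the 20% allowance is to be met in full, the target is 45 per group, 90 in total. That means two more patients. It also means rewriting the allocation procedure in the Randomization section, which draws exactly 88 numbers and splits them 44 and 44, so it would have to be done before allocation.

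Either of the first two options makes the stated figures slightly less favourable and changes nothing else in the design.

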### Randomization

We seek to enroll 88 eligible BC patients during a 3-month recruitment period. The patients will be provided identifiers based on the enrollment order and will be randomly assigned to the intervention or usual groups. A random number Table [28] will be used to divide the 88 patients into two groups at a 1:1 ratio. We will start from the numbers in row 5 and column 6 of the random number table, and random numbers will be selected in turn from left to right. If the exact number is encountered, it will be skipped, and the following number will be skipped until 88 different numbers are collected. All the numbers will then be arranged from small to large, with patients with 44 smaller numbers assigned to the control group and those with the 44 larger numbers assigned to the intervention group. The random sequence will be unknown to the remaining research members except the statistician.

### Blinding

This is a multidisciplinary intervention on dietary management for BC patients, and the BC patients and intervention providers will know the group assignments. Because three face-to-face training sessions for MDT members will be conducted before the intervention is implemented and patients need to receive eight diet-related health education sessions, blinding patients and intervention providers may be challenging. Thus, a single-blinded design will be used, in which the statisticians who analyze the data are not aware of the group assignments.

### Intervention

The intervention protocol was designed according to the Dietary Guidelines for Chinese Residents, National Comprehensive Cancer Network (NCCN) clinical practice guidelines for BC, and the World or American Nutrition Guidelines. The average daily diet should include more than 12 kinds of food or more than 25 kinds of food with reasonable collocation, including cereals and tubers, vegetables and fruits, livestock, poultry, fish, eggs, milk and legumes; however, a balanced dietary pattern of cereals should be followed. According to the Chinese food Pagoda, daily intake of 1500–1700 ml of plain drinking water, less than 5 g of salt, and 25–30 g of oil will be encouraged. Daily intake of cereals should be limited to 200 to 300 g. Daily consumption of vegetable and fruit should be 300–500 g and 200–350 g, respectively. A total of 120–200 g of animal-based foods, including one egg per day, should be consumed. The amount of milk and dairy products should be 300–500 g, and that of soy and nuts should be 25–35 g per day. Conversely, the consumption of excessive amounts of sugar-sweetened beverages, fatty, smoked and preserved meats, and prepackaged foods should be avoided, as these food groups are not beneficial for health [29, 30]. In addition to clinical insights, cognitive, psychological, and behavioral perspectives are equally crucial for DMB. Therefore, we also conducted a scoping review of the performance of DMB interventions and the key elements, adding to the exploration of influencing factors based on the ITHBC. Later, expert consultation methods and patient pilot tests were used to revise and determine the final version of the intervention.

Before the intervention, it will be necessary to establish a MDT team and clarify the division of work to ensure the quality of the intervention. We reviewed the literature on multidisciplinary interventions as comprehensively as possible and combined the characteristics of DMB in BC patients; the MDT providing this intervention will comprise oncologists, clinical nurses, dietitians, TCM practitioners, psychologists, and other research members. The detailed core tasks of team members are illustrated in Fig. 4.

**Fig. 4 Fig4:**
[figure not shown]
The flow chart and core tasks of the team members in this multidisciplinary early intervention. MDT: multidisciplinary team; TCM: traditional Chinese medicine

### Division of work and roles of MDT members in the multidisciplinary early intervention

Oncologists: This group will comprise 4 oncologists from the oncology department or breast surgery department of the hospital. Before the intervention, one oncologist will be responsible for contacting potential participants and assisting with patient recruitment. Another oncologist will provide professional information about the disease and chemotherapy during the intervention. The remaining two oncologists will provide information on healthy weight and adequate food intake according to the patients’ BMI categories and nutritional status and help them to develop individualized management goals.Clinical nurses: This group will comprise a total of 4 nurses. One nurse will assist with patient recruitment before the intervention. During the intervention, one nurse will be responsible for delivering knowledge about coping with adverse reactions and strategies related to dietary self-management, another nurse will provide psychological support, and the last nurse will assist oncologists in formulating targeted diet management goals for patients with different conditions.Dietitian: One dietitian will provide professional dietary and nutritional information and demonstrations, such as common dietary misunderstandings of BC patients during chemotherapy (excessive intake of supplements, replacing normal intake of health care products with three meals, eating only vegetables and no meat, supplementing nutrition by drinking more soup, etc.), the relationship between hormones and diet, correct dietary intake (assessed by a dietitian considering patient age, sex, energy and nutrient needs, physical activity level and the presence of specific pathologies), and scientific methods of weight management (according to the patient’s physical characteristics, a scientific program will be provided to monitor and record food and water intake on the day of weight management). The core elements include reducing caloric intake, increasing the liquid diet appropriately, and controlling hunger.TCM practitioners: One TCM practitioner in the group will convey scientific information on nutritional supplements and dietary replacement from the perspective of TCM, as well as food therapy practices and precautions, which are of great concern to Chinese patients.Psychologist: One psychologist will be responsible for providing professional knowledge, including enhancing self-management confidence, providing treatment self-regulation education, training in social support seeking, and outcome expectation training. Moreover, patients will be led in playing games such as “identifying automatic thoughts, testing hypotheses, examining evidence, identifying alternative thoughts, defending counsel, and challenging wrong, extreme thoughts”.Other research members: Two trained statistical professionals will be primarily responsible for patient recruitment and randomization before the intervention. The other two team members will collect all the data from baseline to follow-up. A statistician will also analyze the data.Team initiator and coordinator: The initiator of this intervention is the oncology department direct, who has rich clinical experience and professional scientific research ability. The coordinator is a nurse with a doctoral degree who organizes and coordinates each MDT meeting, reports to patients, and performs preintervention preparations.

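### The same two people recruit and randomise from a list whose rule is printed, and the text does not separate the list-holder from the blinded analyst

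*Protocol article*

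**What the plan says.** All places are in the Methods/design part of the Protocol article.

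- **Division of work and roles of MDT members**, paragraph on other research members: "Two trained statistical professionals will be primarily responsible for patient recruitment and randomization before the intervention". Two further members collect the data. Then: "A statistician will also analyze the data". One oncologist and one nurse help with recruitment.
- **Randomization**, how the list is made: "We will start from the numbers in row 5 and column 6 of the random number table". Reading goes from left to right, repeats are passed over, and 88 distinct numbers are kept and ranked, with "patients with 44 smaller numbers assigned to the control group and those with the 44 larger numbers assigned to the intervention group". Patient identifiers follow the order of enrolment.
- **Randomization**, who knows it: "The random sequence will be unknown to the remaining research members except the statistician".
- **Blinding**: "the BC patients and intervention providers will know the group assignments". The only blinding claimed is this: "a single-blinded design will be used, in which the statisticians who analyze the data are not aware of the group assignments".
- **Primary outcome**: the DMBQ, which patients complete themselves.

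**The concern.** When patients and providers know the arm and the patient reports the outcome, concealing the next allocation from those who enrol patients is the main remaining protection against selection bias. Here the people mainly responsible for recruitment are also responsible for randomization, and the list follows a rule set out in the article. A recruiter who knows that the next place is in the intervention arm could, without intending harm, enrol a keen patient now and leave a reluctant one for later. Motivation to manage one's diet lies close to what the DMBQ measures, and it is not among the baseline characteristics listed under Demographic and clinical information.

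The second issue is the label single-blinded. It rests on one role, the analysing statistician, and the Randomization section lets a statistician know the sequence.

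**Working it through.** No figure in the plan rests on this point, so there is none to reproduce. The check compares the sections and adds two small calculations.

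**1. Who could hold the list.** The roles section names five other research members: two statistical professionals (recruitment and randomization), two data collectors and one statistician (analysis). No one is described as holding the list while neither recruiting nor analysing.

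**2. Who is the statistician that knows the sequence?** Two readings are possible.

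- *The analyst.* Then the analyst holds the sequence and the Blinding section fails. The recruiters would be among those kept unaware, yet they are responsible for randomization and the printed rule is open to them.
- *One or both of the randomising professionals.* Then the analyst can be blind, but the sequence lies with the pair who recruit.

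Each reading leaves one safeguard open. A sound arrangement, with one of the pair holding the list and the other recruiting, is possible but is not stated.

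**3. Can the list be rebuilt?** The article gives the citation of the table, the starting cell, the direction, the handling of repeats, the ranking rule and the link to enrolment order. It does not give the table itself or the number of digits read at each step. If numbers come from M equally likely values, the expected number of draws to reach 88 distinct ones is M × [H(M) − H(M − 88)], where H(k) = 1 + 1/2 + … + 1/k.

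- Two digits, M = 100: 100 × (5.187 − 3.103) ≈ 208 draws.
- Three digits, M = 1000: 1000 × (7.4855 − 7.3934) ≈ 92 draws.

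This can be done by hand. For someone with the table, each digit width gives one candidate list, so only a few candidates exist.

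**4. What the list adds.** Whoever has the correct list knows 88 of 88 allocations. Pure guessing gets 44 right. Someone without the list who sees past allocations and knows the 44:44 total would expect, with n = 44, n + [4^n / C(2n, n) − 1] / 2 = 44 + (11.79 − 1) / 2 ≈ 49.4 correct. A simulation of 20,000 lists also gave 49.4. The fixed total alone therefore gives little away; the exposure comes from access to the list or its rule.

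**5. Can the knowledge be used?** Yes. One inclusion criterion, fitness of body and mind for the intervention, is a judgement. The first session may fall at any of two, four or six admissions for planned courses of 4, 6 and 8 cycles, so an approach can be deferred and the patient's place in the enrolment order changed.

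**6. Could all 88 be enrolled before anyone is allocated?** That would reduce the exposure, but it fits the schedule poorly. Session 1 takes place at one admission, sessions 2 to 4 in the next three weeks at home, and session 5 at the next admission, so admissions are about 3 + 1 = 4 weeks apart. A 4-cycle patient must start at her first or second admission, that is, within about 4 weeks of the first. Recruitment runs for 3 months, about 13 weeks. A 4-cycle patient enrolled early cannot wait for the last enrolment.

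**The case against.** The strongest defence is that the Randomization section does withhold the sequence from everyone outside one role, and that a journal article commonly leaves the means of release, such as envelopes or a central service, to the full protocol. This stands, and the absence of such a device is not the complaint. The sentence on duties also does not say that each of the two people does both tasks. That is fair too, but it does not say that they are split.

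Several stronger conclusions are tempting, and the documents do not support them.

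- *Allocation is unconcealed.* This is an inference. It is a risk for the recruiting statistical staff, not an established fact for the whole team.
- *Randomization and Blinding contradict each other.* They do so only if the person who knows the sequence is the analyst. The roles section lists the analyst separately, so two people may be meant.
- *All 88 allocations are known to any reader.* That needs the cited table, its layout and the digit width. The wording on repeats is also unclear.
- *A stated bias.* One could suppose that 10% of each arm is shifted by 1 SD in opposite directions, giving 0.10 + 0.10 = 0.2 SD. Both inputs are invented, and 1 SD of motivation need not be 1 SD of DMBQ.
- *Analysis cannot repair it.* This is too absolute. The DMBQ is measured at T0 and the analysis includes the group-by-time interaction, so a stable difference between arms would show at baseline and largely cancel. A difference in how patients change over time would remain.

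**Conclusion.** The point holds as a fault in the stated assignment of duties. Recruitment and randomization lie with the same two people, the list follows a printed rule tied to enrolment order, and nothing separates the person who knows the sequence from the analyst whose blindness is the trial's only blinding. Recruiters who hold the list, or anyone with the cited table, could know or largely reconstruct upcoming allocations, and the single-blind claim is not secured.

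The conclusion assumes that the article describes the procedure as it will be run and that patients are allocated as they enrol, which the schedule favours but the text does not state. The size of any resulting bias cannot be estimated from the documents, and none is claimed. The matter should still be put right, because it bears on the validity of the primary comparison.

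**What to change.** Separate three roles among the staff already named.

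1. One of the two statistical professionals, who neither recruits nor analyses, generates a new list from an unpublished start point or seed, holds it, and releases each arm only after consent and the T0 assessment are logged.
2. The other statistical professional recruits, with the oncologist and nurse who already assist. Neither that professional nor the assistants see the list.
3. A separate analysing statistician receives the arms coded A/B and never the sequence.

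Amend the Randomization, Blinding and Division of work sections to say so, and remove the fixed starting cell. If the analyst already holds the sequence, drop the label single-blinded. If allocation is already complete, state who held the list, who recruited and who analyses, so that readers can judge the risk.

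The cost is a reassignment of duties and a short amendment. No new staff are needed. Blocking or stratification may be worth considering for other reasons, but this point does not require them.
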